### Management, implementation and masking

All the centres have geriatric units and a rehabilitation team that includes a physiatrist, kinesiologist, occupational therapist, and speech therapist. All centres have delirium prevention protocols, one of them with formal research in the implementation of nPPD and use of the software (pilot studies) [12, 13]. Each centre has a specific coordinator and implementing staff. All care providers will take an online course in non-pharmacological management of delirium that will be led by a multidisciplinary research team (physicians, nurses, occupational therapists, and engineers). This will be conducted before recruitment to achieve a homogeneous standard of treatment. In addition, they will participate in telematic meetings to disseminate information, get feedback to increase adherence.

When the patient signs the informed consent, the recruiter will give notice to an independent statistician who will make the random assignment and inform the tablet coordinator via text message, the coordinate will be in charge of installing or not the PREVEDEL software in the tablet according to the assigned group. This person will not have any contact with the patients. A healthcare professional (doctor or occupational therapist) will deliver the tablet and train the patient on how to use it.

The enrollers, evaluators, and healthcare personnel (nurses, physical therapists, physicians, occupational therapists) will be blind to the group assignments. Both groups will receive a tablet of the same dimensions and with the same basic applications. However, blinding the patient is not possible, as when exploring the tablet, he or she will recognise whether or not it has the PREVEDEL program included. To reduce this bias, the staff who delivers the tablet to the patients encourages both groups to use its different basic applications, that they access the internet, and that any questions they may have about its use should be addressed to the tablet coordinator so that the evaluators or healthcare personnel remain blinded.

The time between the assignment and delivery of the tablet will between 4–12 h in all participating centres. This variable will be measured for later analysis.

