B)Use a mobile device. We will use an Alcatel OneTouch Pixi-3 10 tablet which will be delivered daily to each patient between 9:00 am and 8:00 pm, with nighttime pickup (8:00 pm to 09:00 am), so the patient can rest and to charge the device. On the first day, a previously trained health professional will deliver the tablet and train the patients in its use, taking 10–15 min. The day after the tablet is delivered, the same person will go to the patient's room to check if he or she has any questions or problems with its use. Both groups are advised to use the tablet three times a day, for at least ten minutes each time.

To evaluate patient adherence and how the tablet is used, both groups will have an application installed in their devices that will allow them to keep track of the duration of use and applications used.

C)The control group will receive the standard delirium prevention measures outlined above, plus the *use of a mobile device without delirium prevention software* for five days (Control Group: nPPD package, without PREVEDEL).D)The experimental group will receive the standard delirium prevention measures, plus the use of a mobile device with PREVEDEL software for five days (experimental Group: nPPD package, with PREVEDEL).E)The PREVEDEL software was designed and evaluated in a previous study in Chile. It proved to be highly accessible and feasible to improve access to nPPD in hospitalised older adults and showed its possible effect in decreasing the incidence of delirium [12].

To define the software content, a search was carried out in the literature of systematic reviews on non-pharmacological prevention of delirium. The data were reviewed, and the multidisciplinary team chose specific interventions based on their evidence and the feasibility of their incorporation into the software. A literature search was conducted to define the design characteristics of the software and to optimise accessibility for older adults. The data were reviewed, and the multidisciplinary team selected specific design features based on their clinical experience, the technical feasibility to be incorporated into the software, and the opinion of the older adults who participated in the software development.

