The software developed was organised into several modules for easy access, which include:A)Desktop module: this is the first screen the user faces when the software is turned on. It continuously delivers information for temporal and spatial reorientation and allows access to other modules.B)The exercise module contains 12 physical activity videos guided by physical therapists, which can be easily performed by older adults. All exercises are focused on functional activities.C)Games module: includes eight cognitive activities to stimulate attention, memory, and executive function. Colloquial names were selected to improve accessibility. Two different categories of difficulty were considered, according to the patient's level of education based on the above data [14].D)The documentary module contains short videos intended to be a tool for cognitive stimulation, an entertainment activity during free time, and a tool to educate about delirium.E)Alert module: a series of pre-set alerts are displayed during the use of the software. These include the promotion of sensory support measures (glasses, hearing aids), assessment of pain level, and sleep recommendations, with a customisable frequency.F)Configuration module: allows software customisation. It is possible to configure patient data, including educational level, the use of sensory support, and restriction of patient movement if indicated. Access to this module can be password-protected. Healthcare personnel, especially nurses, can use this module to customise the software according to each patient's profile. For example, if the patient has an indication for absolute rest, it is possible to hide all physical activity videos, and if there is a ban on aerobic activity, only exercises with low metabolic demand are shown.G)Registration system. The software keeps a complete record of its use, including the total duration of use and the duration for each module. It also records the number of correct or incorrect answers for cognitive games.

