### Randomisation

Randomisation will be performed using computer-generated random permuted blocks using a centralised, secure, Web-based randomisation service. A computer will assign blocks of ten for each centre so that in each of the four participating centres, there will be a similar number of patients in each group.

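### Ward staff are declared blind although the protocol gives doctors or occupational therapists, and potentially nurses, tasks that reveal the arm; evaluator blinding is not contradicted but is unguarded

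*Protocol article*

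**What the plan says.** Under Management, implementation and masking, the protocol article declares: "The enrollers, evaluators, and healthcare personnel (nurses, physical therapists, physicians, occupational therapists) will be blind to the group assignments". It concedes that patients cannot be blinded, because they will notice whether PREVEDEL is present.

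Four other statements bear on this:

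- **Delivery and training** (same section): "A healthcare professional (doctor or occupational therapist) will deliver the tablet and train the patient on how to use it". Interventions, part B, says that on day one "a previously trained health professional will deliver the tablet and train the patients in its use, taking 10–15 min", and that the same person goes back the next day to the patient's "room to check if he or she has any questions or problems with its use".
- **Configuration** (Interventions, software modules): "Healthcare personnel, especially nurses, can use this module to customise the software". Only experimental tablets carry this software. The module can be password-protected.
- **Installation** (masking section): the tablet coordinator learns the allocation and installs the software or not. The next sentence reads: "This person will not have any contact with the patients".
- **Safeguard** (masking section): patients are told that "any questions they may have about its use should be addressed to the tablet coordinator", with the stated purpose of keeping evaluators and staff blind.

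The primary outcome is delirium and subsyndromal delirium by CAM, applied twice daily for five days (Outcomes). The tablet is with the patient from 09:00 to 20:00 (Interventions, part B).

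**The concern.** Both arms receive the same ward package: environment, mobilisation, correction of sensory deficits and medication management. Staff who know the arm may deliver that package differently, consciously or not. Blinding ward staff is the stated protection against this performance bias. If the procedures defeat it, a difference between arms can no longer be attributed to the software alone, and a report that repeats the masking statement would claim a property the trial lacks.

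A second risk is ascertainment. The CAM is a judgement. Eligibility treats a single core element as enough to exclude a patient, so a borderline rating could decide a subsyndromal event if the same rule is used for the outcome. An evaluator who knows which patients have the prevention software could score them more leniently. This risk depends on evaluators learning the arm. The text does not say that they do, but it gives little to prevent it.

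**Working it through.** **1. Stated blinding against assigned tasks**

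| Group | Stated status | Task in the text | Compatible? |
|---|---|---|---|
| Doctors, occupational therapists | Blind | Deliver the tablet, train for 10–15 minutes, return next day | No, for those who do it |
| Nurses | Blind | Able to configure PREVEDEL for individual patients | No, if the capability is used; nothing withdraws it for the trial |
| Physical therapists | Blind | No tablet task | No contradiction |
| Enrollers | Blind | Notify the statistician after consent | No contradiction |
| Evaluators | Blind | No tablet task | No contradiction, but unguarded |

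The first row follows from the protocol's own reasoning. It accepts that a patient exploring the tablet will recognise the program, and it describes the desktop module as the first screen when the software is turned on. Someone teaching the patient to use the device must see it too.

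**2. The safeguard**

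- Routing questions to the coordinator presupposes that handling them can unblind.
- The coordinator, read naturally as the person meant in "This person will not have any contact with the patients", is not in contact with patients.
- The professional who delivers the tablet is the one sent back to ask about questions and problems.

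These three statements cannot all be followed as written.

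**3. Evaluators**

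Patients are unblinded, the tablet is in the room for 11 hours a day (09:00 to 20:00), and the CAM is done twice daily. The article gives no CAM times, does not say who applies the CAM, and does not separate evaluators from tablet staff.

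**4. Sensitivity of the primary test to differential scoring**

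First, the plan's own figure. With p₁ = 0.20, p₂ = 0.08, two-sided α = 0.05 and 80% power (Study sample), d = 0.12 and the mean proportion is 0.14:

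- n = [1.960·√(2·0.14·0.86) + 0.8416·√(0.20·0.80 + 0.08·0.92)]² / 0.12² = (0.9618 + 0.4068)² / 0.0144 ≈ 130.1, so 131.
- With continuity correction: (130.1/4)·[1 + √(1 + 4/(130.1·0.12))]² ≈ 146.3, so **147**, as stated.
- Exact Fisher power at 147 per arm is 81.8%.

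Next, assume no true effect, a risk of 20% in both arms, and a proportion m of PREVEDEL-arm cases missed. The observed risk in that arm is 0.20·(1 − m). The rejection rate is the sum, over all pairs of binomial counts with n = 147 per arm, of the pair's probability where the two-sided Fisher p is at most 0.05. The true expected number of cases per arm is 147·0.20 = 29.4.

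| m (assumed) | Cases missed (29.4·m) | Observed risk | Apparent risk ratio | Rejection rate |
|---|---|---|---|---|
| 0 | 0 | 20% | 1.0 | 3.6% |
| 10% | 2.9 | 18% | 0.9 | 5.4% |
| 20% | 5.9 | 16% | 0.8 | 11.4% |
| 30% | 8.8 | 14% | 0.7 | 23.0% |

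The miss rates are not in the documents.

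**5. Block size (secondary)**

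Randomisation states: "A computer will assign blocks of ten for each centre". For a block with five allocations per arm, best guessing with every earlier allocation in the block known gives 5 + 2⁹/C(10,5) − ½ = 5 + 512/252 − 0.5 = 6.53 correct per ten (65%). On average 10/6 = 1.67 allocations per block are fully determined. Both figures are upper bounds.

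**The case against.** The strongest reply is that the masking section distinguishes the staff who deliver the tablet from the evaluators and healthcare personnel who are to remain blind, and says each centre has implementing staff. Deliverers may then be study staff and the blinded group the treating team, so that the clash is only loose wording about professions. That reading is possible. But the masking statement lists physicians and occupational therapists without exception, and the deliverer is defined by those same professions. The coordinator conflict remains on either reading.

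Several further objections stand, and they limit the point:

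- **Nurses.** The text says that they can use the module, within a description of software features. A reader might infer that nurses will configure every experimental tablet; the article does not say so.
- **Evaluators.** A reader might infer that their blinding is contradicted too, or that the CAM results will be biased. No tablet task is assigned to them, and nothing says the PREVEDEL screen is showing during a CAM. Tablets have the same dimensions and basic applications in both arms. Naming the CAM assessors is also detail that an article may leave to the full protocol.
- **Magnitude.** At a 10% miss rate the rejection rate of 5.4% is close to the nominal 5%; part of the contrast comes from the conservatism of Fisher's test (3.6%).
- **Block guessing.** A reader might infer that recruiters can predict allocations. The article gives enrollers no access to past allocations, and an independent statistician assigns after consent.

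**Conclusion.** The claim that healthcare personnel are blind is not delivered by the procedures described. It is contradicted for the doctors or occupational therapists who handle the tablet and is incompatible with the configuration role open to nurses. The safeguard is inconsistent with the rest of the text. The direct consequence is exposure to performance bias, whose size the documents do not allow one to estimate.

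Ascertainment bias in the CAM is an unguarded risk and not a demonstrated flaw. The rejection rates of 5.4% to 23.0% rest on assumed miss rates of 10% to 30%, a 20% risk in both arms and 147 patients per arm. They show how sensitive the primary test is and predict nothing. The sample size and the planned test are unaffected. Predictable allocation is not established, since the 65% and 1.67-in-ten figures require complete knowledge of the current block.

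**What to change.** 1. State that the deliverer/trainer, the tablet coordinator and any staff who configure the software are unblinded. Bar them from CAM, FIM and MoCA assessment and from recruiting.
2. Have the tablet switched off and out of sight before each CAM.
3. Have evaluators record their guess of the allocation on day 5, and report it by arm.
4. Withdraw the claim that ward staff are blinded, and describe the trial as evaluator-blinded.
5. Reconcile Interventions (part B and the configuration module) with Management, implementation and masking on who configures the software, who answers patient questions, and whether the coordinator meets patients. How movement restrictions are set in the software is a clinical matter for the investigators; the text need only say who does it and that they are unblinded.
6. Optionally, use randomly varied block sizes within centre in place of fixed blocks of ten.

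The cost is revised wording in the protocol and the manual of procedures, one extra field on the day-5 form and, for item 6, one setting in the randomisation service. No extra staff are needed, provided the roles can be kept apart among existing staff at each centre. The endpoint, sample size and analysis stay as they are. The downside is that the claim of blinded ward staff is lost.

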### Analysis and statistical methods

The results will be analysed with the intention to treat. For the descriptive analysis of the variables, we will use the mean (standard deviation), median (25–75 percentile), or proportions as appropriate to the type and distribution of the data.

Analytical Statistics: For the primary outcome, a comparison of proportions between patients who develop delirium and subsyndromal delirium in both groups will be made, using Fisher's exact test, and as a measure of efficacy, an odds ratio with 95% confidence interval will be estimated. If there is any baseline variable that is not matched by the randomisation, efficacy analyses will be conducted using logistic regression with the main variable being the treatment, and the adjustment variables will be those that the randomisation would not have been able to match. Additionally, to compare the effect of the intervention over time, a time-to-event analysis will be performed using the Kaplan-Maier procedure and then the Cox regression model to adjust for baseline variables and the presence of the intervention. For the secondary outcomes, the Fisher's exact test or t-test will be used, as appropriate for the type and distribution of the data. Linear regression or multivariate logistics will also be performed, as appropriate, to evaluate the impact of the intervention, adjusting for the input covariates. A bilateral *p* < 0.05 significance level will be used for all analyses.

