### Participants

The research is developed in four hospital centres of similar complexity located in Santiago, Chile. These are: Hospital Clínico de la Universidad de Chile (HCUCH), Hospital San Juan de Dios, Clínica Las Condes, and Hospital Santiago Oriente [name]. Two are public institutions and two are private institutions. Patients hospitalised in general wards (Geriatric and Internal Medicine Units) and Intermediate Care Units. The units serve older adults admitted for acute pathologies, in the intermediate care unit patients can receive non-invasive ventilation, high-flow nasal cannula, and low doses of vasopressors.

We will include patients 65 years or older, hospitalised less than 48 h prior in a general ward or the intermediate care unit of four participating centres. Patients with full or syndromal delirium (Confusion Assessment Method-[CAM] + or presence of one core element) history of dementia (Alzheimer’s Disease-AD8 greater than 2 points), and non-Spanish speaking patients will be excluded.

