### Study sample

Local and literature data were evaluated to calculate the sample size [1, 13]. A delirium status prevalence of 20% is estimated in the control group and a decrease in prevalence to 8% in the intervention group is expected. In this way, with a power of 80%, and an alpha of 0.05 bilaterally, 147 patients will be enrolled in each group. If we add to this a 10% loss of follow-up, the overall sample size will be 320 patients (See flow chart in Fig. 1).

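### Randomisation is blocked within four centres, but the primary test is an unstratified Fisher's exact test: a modest and avoidable loss of efficiency, not of validity

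*Protocol article*

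**What the plan says.** The Randomisation section of the protocol article stratifies allocation by hospital: "A computer will assign blocks of ten for each centre". The Participants section describes the four hospitals: "Two are public institutions and two are private institutions". It gives no event rates by centre.

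The section on analysis and statistical methods compares proportions between the arms with Fisher's "exact test, and as a measure of efficacy, an odds ratio with 95% confidence interval will be estimated". No stratum or centre term is named. Logistic regression is added for the primary outcome only if some baseline variable turns out to be unbalanced, and it then adjusts for the unbalanced variables. The Cox model and the secondary regressions refer to baseline variables or covariates in general, without naming centre.

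The Study sample section fixes the planning figures: "A delirium status prevalence of 20% is estimated in the control group", "a decrease in prevalence to 8% in the intervention group is expected", "with a power of 80%, and an alpha of 0.05 bilaterally", and "147 patients will be enrolled in each group".

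**The concern.** A factor used to stratify the randomisation normally belongs in the primary analysis. Here the adjustment rule works the other way round: it brings in only what randomisation left unbalanced, so the one factor balanced by design is the one it would normally omit.

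Centre could plausibly matter. The hospitals are a mix of public and private, they recruit from general and intermediate care wards, and one has earlier research experience with the prevention programme and the software. If risks differ between centres, a pooled 2×2 table leaves that variation in the comparison. Power is then lower than it need be, and the pooled odds ratio sits closer to 1 than the within-centre odds ratio. Fisher's test is also conservative in its own right, so the two effects must be separated before either is blamed.

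**Working it through.** **Inputs.** From the Study sample section: risks of 20% and 8%, two-sided alpha 0.05, power 80%, 147 per arm. Planned odds ratio = (0.08/0.92)/(0.20/0.80) = 0.348. Assumptions, because the protocol gives neither: near-equal centres (37/37/37/36 per arm), and control risks by centre that are (a) all 20%, (b) 10/15/25/30%, (c) 5/10/25/40%, with a common within-centre odds ratio of 0.348.

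**1. Reproduce the plan's figure.** With pooled variance under the null and mean risk 0.14:

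n = [1.960·√(2·0.14·0.86) + 0.842·√(0.20·0.80 + 0.08·0.92)]² / 0.12² = 130.07, so 131.

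With the continuity correction, n′ = (n/4)·[1 + √(1 + 4/(n·0.12))]² = 146.3, so **147**, the stated figure. The correction approximates Fisher's test, so the sample size and the planned test agree. By exact enumeration, Fisher reaches 80% power at 142 per arm. At 144 per arm (320 less 10%, "If we add to this a 10% loss of follow-up, the overall sample size will be 320 patients") it has 80.8%.

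**2. Size and power at 147 per arm.** Fisher and the pooled chi-square were enumerated exactly from the binomial counts. The centre-stratified CMH test, without continuity correction, was simulated.

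| Control risks by centre | Fisher power | Pooled chi-square power | CMH power | Fisher size | CMH size |
|---|---|---|---|---|---|
| (a) all 20% | 81.8% | 85.9% | 85.6% | 3.6% | 5.0% |
| (b) 10/15/25/30% | 80.1% | 84.6% | 85.0% | 3.3% | 5.0% |
| (c) 5/10/25/40% | 76.3% | 81.5% | 83.5% | 2.6% | 5.0% |

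Short simulations of Fisher's size in (c) scatter around the exact value, at about 2.3 to 2.7%.

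**3. Split the gap.** Fisher to CMH is about 4, 5 and 7 points. Fisher to pooled chi-square, which also ignores centre, is 4.2, 4.5 and 5.2 points: this part is discreteness. Pooled chi-square to CMH is −0.3, 0.4 and 2.0 points: this part is centre. If the pooled chi-square uses the N−1 variance, to match CMH, the centre part is 0.1, 0.9 and 2.5 points.

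**4. The estimate.**
- In (b) the mean risks are 0.1993 and 0.0818, so the pooled odds ratio is (0.0818/0.9182)/(0.1993/0.8007) = 0.358.
- In (c) they are 0.1986 and 0.0861, so it is (0.0861/0.9139)/(0.1986/0.8014) = 0.380.

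The expected standard error of the log odds ratio, crude against centre-adjusted, is 0.367 and 0.367 in (a), 0.365 and 0.370 in (b), and 0.359 and 0.376 in (c). Adjustment does not narrow the interval; it moves the estimate away from 1 by more than it widens the error. In (c), |ln 0.380|/0.359 = 2.69 against |ln 0.348|/0.376 = 2.81.

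**5. A detail for the fix.** CMH with a continuity correction gives 81.1%, 80.4% and 78.6% power, so the correction removes most of the gain.

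**The case against.** The strongest objection is that little is lost and nothing is invalid. The error rate is below 5%, the sample size was in effect calculated for Fisher's test, and planned power fails only in scenario (c), where control risk varies eightfold between centres. The protocol gives reason to expect less spread: it describes the hospitals as comparable in complexity, all have geriatric units and delirium protocols, and common training precedes recruitment. All of this stands, and it limits the point to efficiency.

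It can also be said that the article condenses a fuller protocol and that an analysis plan may name centre. The article does not call the odds ratio crude; that is inferred from its pairing with Fisher's test. This is fair, but the primary test itself is fixed in the text, and so is an adjustment rule that would normally pass centre by.

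A reader might infer more than the document supports:

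- *The whole power gap comes from ignoring the blocking.* Step 3 shows that most of it comes from Fisher's discreteness.
- *The trial is underpowered, or power is thrown away.* The 147 matches the continuity-corrected formula, and Fisher has 81.8% power when centres are alike.
- *The odds-ratio interval is too wide.* The crude interval is as narrow as the adjusted one, or narrower.
- *The odds ratio is an error because the hypothesis is stated in risks.* It is a legitimate measure and matches the planned logistic model. Preferring a risk scale is a choice.

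**Conclusion.** The point holds as a modest loss of efficiency. The primary analysis leaves out the stratification factor, and the adjustment rule would normally keep it out. Changing from Fisher to a centre-stratified test gains about 4 to 7 points of power at 147 per arm. Of this, about 0 to 2 points (2.5 at most, depending on the chi-square variance used) belong to centre, and the rest to Fisher's discreteness. Stated power is missed only with widely differing centres, and there the pooled odds ratio drifts to 0.38 against 0.348 within centres. That drift is a property of pooling odds ratios over unequal risks; it is not confounding, since the arms are balanced within centre.

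The reproduction of 147 and Fisher's size and power with equal centres need only the protocol's figures. The share due to centre rests on assumed centre risks, near-equal centre sizes and a common odds ratio.

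**What to change.** In the section on analysis and statistical methods, make the primary test centre-stratified: either Mantel-Haenszel, stating that no continuity correction is applied, or logistic regression with treatment and centre as factors. Include centre whatever the observed balance. Report the centre-adjusted odds ratio with its 95% confidence interval, and keep the pooled Fisher's test as a sensitivity analysis. Optionally add a centre-adjusted risk difference, so that the result can be read directly against the 20% versus 8% hypothesis.

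The cost is a few sentences of wording, settled before anyone sees outcomes by arm. It needs no new data and no extra patients.

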### Outcomes

A)Primary outcome:

To evaluate the incidence of delirium and incidence of subsyndromal delirium by applying the CAM [15] twice daily during five days of hospitalisation.

The incidence of basal delirium will be determined before the software is implemented in a group of patients enrolled prospectively with the same inclusion/exclusion criteria and delirium assessment protocol.

B)Secondary outcomes:Duration of delirium (days) and density of delirium (incidence x duration) will be assessed with the CAM.Level of independence in basic activities of daily living on day 5, will be assessed using the Functional Independence Measure (FIM), this instrument evaluates independence in 18 activities of daily living (13 motor and five cognitive items). The scale has seven levels (1–7, from lower to higher levels of independence). The motor FIM score ranges from 13–91, cognitive FIM from 5–35 points, and total FIM from 18–26 points; higher scores indicate greater independence [16].Cognitive level on Day 5 assessed using the Montreal Cognitive Assessment. The test evaluates attention and concentration, executive functions-memory, language, visuoconstructional skills, conceptual thinking-calculations, and orientation. It has Chilean validation in the population over 60 years of age [17].Hospital stay (days).90-day mortality.Duration of device use will be compared using the internal device registration.Presence of sleep disorders and headache will be evaluated using a self-reporting instrument in both groups. The doctor in charge of the patient will be informed for management.Adherence to the nPPD programme will be evaluated in the four participating centres before and after training in prevention measures. Assessment of adherence to non-pharmacological prevention domains (12 indicators) will be conducted [13].

In addition, socio-demographic data and clinical information will be gathered including The reason for admission, the Acute Physiology and Chronic Health disease Classification System II score, the Sequential Organ Failure Assessment), and the Charlson Comorbidity Index.

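### Observed baseline imbalance decides whether the efficacy analysis is adjusted and for what, and the plan does not say which odds ratio leads

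*Protocol article*

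**What the plan says.** The Analysis and statistical methods section of the protocol article compares the proportions with delirium and subsyndromal delirium "using Fisher's exact test, and as a measure of efficacy, an odds ratio with 95% confidence interval will be estimated". It then sets a conditional rule: "If there is any baseline variable that is not matched by the randomisation, efficacy analyses will be conducted using logistic regression", and "the adjustment variables will be those that the randomisation would not have been able to match". It gives no definition of unmatched, no threshold and no list of candidate variables. It does not say whether the unadjusted or the adjusted odds ratio is the primary result once the rule has fired.

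The Outcomes section says that "socio-demographic data and clinical information will be gathered", including reason for admission, APACHE II, SOFA and the Charlson index. The Randomisation section uses permuted blocks of ten within each of the four centres, but centre is not named as a covariate. The Cox model and the secondary regressions are also adjusted, for sets that are not named.

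**The concern.** Observed imbalance settles both the form of the efficacy model and its covariates. That is a poor selection criterion for three reasons.

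- In a properly randomised trial a baseline difference is chance. It says nothing about prognosis, and adjustment earns its precision from prognosis.
- Centre, the stratification factor, would hardly ever enter the model, because blocking within centre keeps it balanced.
- The unadjusted odds ratio is a marginal quantity and the covariate-adjusted one is conditional. They differ even with perfect balance, so not saying which leads leaves the target of estimation open as well as the precision.

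At stake are freedom to choose after seeing the data, and efficiency given up from data the trial already collects.

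**Working it through.** **1. The plan's own sample size.** Inputs from Study sample: "A delirium status prevalence of 20% is estimated in the control group"; "a decrease in prevalence to 8% in the intervention group is expected"; "with a power of 80%, and an alpha of 0.05 bilaterally, 147 patients will be enrolled in each group". With mean rate 0.14 and difference 0.12:

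- n = [1.960·√(2·0.14·0.86) + 0.842·√(0.20·0.80 + 0.08·0.92)]² / 0.12² = 130.1, so 131 per arm.
- With continuity correction: (130.1/4)·[1 + √(1 + 4/(130.1·0.12))]² = 146.3, so **147**, as stated.

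The planned odds ratio is (0.08/0.92)/(0.20/0.80) = 0.35, a log odds ratio of -1.06. Expected events: 147·0.20 + 147·0.08 = 29.4 + 11.8 ≈ 41. By enumeration, Fisher's test at 147 per arm has 81.8% power and an actual type I error of 3.6% at a 20% rate. With 10% lost from 320 (144 per arm) its power is 80.8%.

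**2. How often the rule would fire.** Assumption, not in the documents: unmatched means p<0.05 on a baseline test. For K independent variables the chance of at least one is 1 - 0.95^K.

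| K | Independent | Correlation 0.3 | Correlation 0.5 |
|---|---|---|---|
| 5 | 23% | 21% | 18% |
| 10 | 40% | 35% | 28% |
| 15 | 54% | 46% | 36% |

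**3. Power and type I error.** Simulation of 4,000 trials per scenario: 147 per arm, marginal rates 20% v 8% (power) or 20% v 20% (type I error), and ten independent normal covariates. Of these, 0, 2 or 3 are prognostic, with the log odds ratio per SD shown. The prognostic strengths are assumptions. The fixed model holds exactly the truly prognostic covariates. Monte Carlo standard error is about 0.4-0.6 points for power and 0.35 for type I error.

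| Prognostic covariates | Rule (Fisher unless triggered) | Rule, logistic in both branches | Fixed model | Loss |
|---|---|---|---|---|
| none | 82.8% | 84.6% | 84.6% | 1.8 / 0 |
| 2 at 0.5 | 83.4% | 85.8% | 87.6% | 4.2 / 1.8 |
| 3 at 0.6 | 82.8% | 84.9% | 88.2% | 5.4 / 3.3 |
| 3 at 0.8 | 83.3% | 85.7% | 91.9% | 8.6 / 6.2 |

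The two losses are against the first and second form of the rule. The first row shows that about 2 points come from the conservatism of Fisher's test and not from covariate selection.

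Type I error was 3.7-4.2% under the rule with Fisher and 4.1-4.9% with logistic regression in both branches. For the fixed model it was 4.3-6.0%, so a little of that model's power comes from using more of the nominal 5%. In a further simulation that added centre to three covariates, the fixed model had 88-91% power and 5.3% type I error, against 84-85% and 3.8% for the rule.

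**4. The two odds ratios.** In the strongest scenario the median log odds ratio was -1.07 unadjusted (odds ratio 0.34) and -1.34 in the fixed model (0.26). Under the rule it was -1.08, because the selected covariates are seldom the prognostic ones.

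**5. Room for choice.** With three covariates at 0.6, Fisher and the adjusted model disagreed on significance in 6.5% of the trials at 20% v 8% in which the rule fired. Taking the smallest p-value from Fisher and imbalance thresholds of 0.05, 0.10 and 0.20 raised type I error from 3.7% to 5.3%.

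**The case against.** The best defence is that Fisher's test and the unadjusted odds ratio are stated without condition, so the logistic model can be read as an added sensitivity analysis. Definitions and covariate lists commonly belong in an SAP, which is not shown. Part of this stands: the missing list and threshold are not findings in themselves. But the article goes beyond silence. It states the selection rule, and an SAP that chose covariates on prognosis would contradict it. Even on the additive reading there are two odds ratios, one with data-chosen covariates, and nothing says which leads.

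A second objection is that the comparison flatters the fixed model, which contains exactly the true predictors at strengths the documents do not give. That stands, and it is why the loss is given as a range that reaches zero for the covariates themselves.

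A third is that 41 events cannot support centre plus several covariates. Simulated type I error of 5.3% for centre plus three covariates does not bear this out, though it does argue for a short list.

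A reader might also infer that the rule inflates false positives or leaves the trial below 80% power. The figures support neither. Type I error under the mechanical rule is below 5%, and even the selective use in step 5 reaches only 5.3%. Power near 70% for Fisher appears only under a smaller effect: for example, a conditional log odds ratio of -1.0 with three covariates at 0.7, 0.5 and 0.5 implies about 20% v 9.3%, not the planned 20% v 8%, which would need about -1.18.

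**Conclusion.** The point holds as a badly fixed rule that should be corrected, not as a threat to validity. Model and covariates depend on chance imbalance, and the leading odds ratio is not identified. Under the stated assumptions the trigger would fire in about 23% to 54% of trials for 5 to 15 independent variables, and less often if they are correlated. It would be too strong to say that the primary result is decided by a coin toss: the number of variables and the test are not in the documents, and Fisher's result is planned in any case.

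The efficiency cost is roughly 4-9 points of power against a fixed prognostic model, or 2-6 if logistic regression is used in both branches. It depends on assumed prognostic strength, and the covariates bring no gain if none is prognostic. Power under the rule stays at about 83-85%. Nor are the baseline data wholly unused, since the Cox and secondary models also adjust.

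**What to change.** Delete the imbalance trigger. Before unblinding, name one primary analysis: logistic regression on treatment, centre and a short fixed list of about three baseline variables already collected, chosen for prognostic value (for example age, APACHE II and Charlson). Keep the list short because only about 41 events are expected. Use the same set in the Cox and secondary models, and keep the unadjusted Fisher comparison and its odds ratio as supportive.

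The cost is a change of wording, with no new data and no change in sample size. There are two small downsides: the primary odds ratio becomes conditional and should be labelled so, and a few parameters are spent on a modest number of events.
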